### Data analysis plan

2.5

#### Power analysis

2.5.1

The sample size calculation was conducted considering the primary between-subjects objective of the study, namely the comparison of suicide risk ratings across the ten participant groups at baseline. Although the study design includes repeated measurements within individuals, due to multiple vignette ratings and a follow-up assessment at two weeks, the power analysis was intentionally restricted to the primary baseline comparison in order to align with standard assumptions for sample size estimation, thus providing a conservative estimate of the required sample size.

The primary outcome for power estimation was operationalized as the vignette-based suicide risk rating expressed on a 1 to 9 scale in the No-C-SSRS condition, treated as an ordinal variable. Accordingly, the sample size calculation was based on a one-way ANOVA comparing the ten independent study groups. Although the 1 to 9 rating scale will be analyzed using ordinal mixed-effects models in the primary analyses, ANOVA will be adopted for sample size estimation as a conventional and conservative approximation for planning purposes when dealing with multi-level ordinal variables treated as approximately continuous. Assuming a small-to-medium effect size (f = 0.20), a two-sided alpha level of 0.05, and a desired statistical power of 80 percent (1 − β = 0.80), G*Power indicated that a minimum of 400 participants would be required to detect overall group differences. Although participants are randomized across two conditions (C-SSRS vs. No-C-SSRS), the primary power estimation focused on detecting between-group differences in suicide risk estimates at baseline. Randomization is expected to be approximately balanced across the ten groups, thereby preserving adequate sample size within each group for primary comparisons. This approach provides a conservative estimate of statistical power, as it does not incorporate the additional information obtained from repeated vignette ratings or from mixed-effects modeling, both of which are expected to increase precision and statistical efficiency.

To account for expected attrition at follow-up, the planned sample size was increased to at least 500 participants. This choice was informed by evidence from a recent study by Kolochowski et al. (20), which used the same set of vignettes adopted in the present protocol and reported a follow-up completion rate of 55.9 percent. Assuming a conservative attrition rate of approximately 40 to 45 percent, an initial sample of 500 participants would result in a final sample of approximately 275 to 300 individuals, which remains adequate for the planned longitudinal and within-subject analyses. The online administration format and broad inclusion criteria further support the feasibility of achieving this sample size.

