#### Baseline assessment

2.3.1

The study procedures and enrollment process are shown in **Figure 2**. During the baseline assessment, participants will be asked to answer sociodemographic questions as well as to indicate their professional and academic background, in order to assign them to a specific study group. Then, participants of each group (i–x) will be randomly assigned to one of the two conditions (C-SSRS *vs.* No-C-SSRS).

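### The 400 participants behind the stated 80% power would all need a 1–9 rating, but only the No-C-SSRS condition gives one; by the plan's own calculation, 500 enrolled gives about 55%

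*Protocol article*

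**What the plan says.** Section 2.5.1 (Power analysis) bases the sample size on the baseline comparison of the ten groups. The outcome for that calculation is the "suicide risk rating expressed on a 1 to 9 scale in the No-C-SSRS condition, treated as an ordinal variable". The method follows: "the sample size calculation was based on a one-way ANOVA comparing the ten independent study groups", with f = 0.20, "a two-sided alpha level of 0.05" and 80% power. The result is that "G*Power indicated that a minimum of 400 participants would be required to detect overall group differences".

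Section 2.3.1 (Baseline assessment) states that "participants of each group (i–x) will be randomly assigned to one of the two conditions". Under the same heading, only No-C-SSRS participants rate on the 1–9 scale. The C-SSRS arm classifies each vignette as low, moderate or high, and the article notes that the instrument yields no continuous score.

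Section 2.5.1 recognises that there are two conditions and answers: "Randomization is expected to be approximately balanced across the ten groups, thereby preserving adequate sample size within each group for primary comparisons". It calls the calculation conservative because repeated ratings and mixed models are left out and are expected to add precision. The total is then raised to at least 500, and the reason given is attrition at follow-up.

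**The concern.** The ANOVA answers the question of how many people with a 1–9 rating are needed. The plan uses the answer as the number of people to enrol across both conditions, although only one condition supplies that rating. The increase to 500 serves a different purpose and does not make up for the split.

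The sentence on balance does not close the gap. If randomisation balances the conditions within each group, it divides each group's usable size by two; it does not preserve it.

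This calculation is the only stated basis for the sample size and it concerns the primary between-subjects objective. The protocol would therefore go forward with a stated power that its own outcome, test and enrolment do not produce together.

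**Working it through.** **Inputs from Section 2.5.1:** k = 10 groups, f = 0.20, alpha = 0.05, target power 0.80, one score per person, minimum 400, planned 500.

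**Assumptions:** 1:1 allocation (the natural reading of random assignment to two conditions, but no ratio is given) and equal group sizes.

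**Formula.** Omnibus one-way ANOVA: df1 = k − 1 = 9, df2 = N − 10, noncentrality λ = N × f². Power is the probability that a noncentral F(9, N − 10, λ) exceeds the central F critical value at upper-tail 0.05. N counts people who have the outcome.

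**Step 1: reproduce the plan.** With N = 400, λ = 400 × 0.04 = 16 and df = 9 and 390. Power is 0.800, and 400 is the smallest N that reaches 0.80. The plan's figure is therefore correct for 400 people with a 1–9 rating, 40 per group.

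**Step 2: apply the split by condition.**

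| Enrolled | With a 1–9 rating | Per group | λ | df2 | Power at f = 0.20 | f detectable at 80% |
|---|---|---|---|---|---|---|
| 400 | 400 / 2 = 200 | 20 | 8 | 190 | 0.435 (0.4349) | 0.286 |
| 500 | 500 / 2 = 250 | 25 | 10 | 240 | 0.546 | 0.255 |
| 800 | 800 / 2 = 400 | 40 | 16 | 390 | 0.800 | 0.200 |

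**Step 3: what six ratings per person could add.** The article does not say whether f = 0.20 refers to a single rating or to a participant's mean. If it refers to a single rating, averaging six ratings with within-person correlation ρ multiplies f by √(6 / (1 + 5ρ)). The article gives no ρ, so a range is shown.

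| ρ | Multiplier | Power, n = 200 | Power, n = 250 |
|---|---|---|---|
| 0.3 | 1.549 | 0.871 | 0.946 |
| 0.5 | 1.309 | 0.710 | 0.827 |
| 0.7 | 1.155 | 0.575 | 0.699 |
| 1.0 | 1.000 | 0.435 | 0.546 |

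The break-even ρ at n = 250 follows from the detectable f. The multiplier needed is 0.2546 / 0.20 = 1.273, and 1.273² = 1.621. Then 1 + 5ρ = 6 / 1.621 = 3.70, so ρ ≈ 0.54. At n = 200 the multiplier needed is 0.2860 / 0.20 = 1.430, its square is 2.044, 1 + 5ρ = 2.935 and ρ ≈ 0.39. If f = 0.20 already describes a participant mean, the multiplier does not apply and step 2 stands.

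**The case against.** The strongest reply is that the planned analysis is not a one-score ANOVA. Section 2.5.2 uses ordinal mixed models on all ratings, and Section 2.5.1 says openly that repeated ratings should add precision. This stands in part. A reader might infer from step 2 that the primary analysis really has 43% or 55% power. The documents do not support that: true power depends on what f refers to and on a within-person correlation that is not given, and step 3 shows that it could exceed 80%. But an unquantified gain cannot be set against a known halving of the number of people, and it cannot support the word conservative.

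A second reply is that the mixed models include condition and use both arms. With all 500 contributing, the same formula gives 0.897. Pooling, however, needs the three-level conversion in Table 1 (Section 2.4.2), which is introduced for the secondary comparison. That is not the outcome named for power. HP 5 in Section 1.1 also expects more agreement under the C-SSRS, so group differences there may be smaller and f = 0.20 cannot simply be carried over.

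Third, the sentence on balance might be taken to claim that randomisation determines the sizes of the ten groups. Read with Section 2.3.1, it more naturally means that conditions are balanced within each group, which is a reasonable expectation. Only the conclusion drawn from it, that group size is preserved, is wrong.

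Finally, 43% belongs to the minimum of 400. The planned size is 500, so 55% is the relevant figure.

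**Conclusion.** The point holds as a mismatch between the powered outcome and the number enrolled. The figure of 400 is right for 400 people who give a 1–9 rating and wrong as a total over two conditions. By the plan's own method, the planned 500 gives about 55% power at f = 0.20, or 80% power at f of about 0.255. The minimum of 400 gives about 43%, or 80% power at f of about 0.286.

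These figures rest on 1:1 allocation, equal groups and one score per person. They show that the stated calculation does not deliver the stated 80%; they do not establish the power of the mixed-model analysis. Nor do they show that the study must enrol 800. That number would be needed only to keep 80% at f = 0.20 on the named outcome with one score per person. The section needs correcting because outcome, test and sample size do not fit together as written.

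**What to change.** Amend Section 2.5.1 in one of these ways:

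- Restate the calculation for the No-C-SSRS arm: about 250 of 500, giving about 55% power at f = 0.20, or 80% power at f of about 0.26. State the allocation ratio.
- Give an explicit repeated-ratings calculation for that arm, saying whether f refers to a single rating or a participant mean, and stating and justifying the within-person correlation.
- If the three-level rating from both arms is meant as the powered outcome, say so and recompute with an effect size justified for that outcome.

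In each case, remove the inference that randomisation preserves the sample size within each group. The expectation of balanced conditions can stay. Drop the description of the estimate as conservative unless a repeated-ratings calculation supports it.

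The cost is one recalculation and some rewording. The stated power or detectable effect becomes less favourable; no extra participants are needed unless the sponsor chooses to keep 80% power at f = 0.20 on the one-score basis.

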### Data access and management

2.6

Data will be managed and stored within the Department of Pathophysiology and Transplantation at the University of Milan and will be accessed exclusively by the study investigators and will not be shared with other operational units. All collected data, including personal data, will be the exclusive property of the University of Milan, and no external parties will have access to them. The questionnaire will be administered through a dedicated link redirecting participants to the Qualtrics platform. Responses will be collected directly through Qualtrics and subsequently organized into a study-specific database. Participation in the baseline questionnaire will be completely anonymous. At the end of the baseline survey, participants will be invited, on a fully voluntary basis, to provide an email address exclusively for the purpose of receiving the follow-up questionnaire link. Providing an email address will not be mandatory for participation in the study, and individuals may complete the baseline survey without leaving any contact information. Contact information will be used solely for follow-up communication and will not be included in the analytical dataset. Following data extraction, study variables and suicide risk estimates results will be entered into an electronic database for statistical analysis. In accordance with applicable data protection regulations (General Data Protection Regulation, EU Regulation No. 2016/679), all collected data will be stored confidentially for a period of ten years within the Department of Pathophysiology and Transplantation at the University of Milan.

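### Raising 400 to 500 offsets a 20% loss, not the assumed 40–45%, and the adequacy claimed for the 275–300 left at follow-up has no calculation behind it

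*Protocol article*

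**What the plan says.** All of the sizing is in section 2.5.1 (Power analysis) of the protocol article.

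- **Basis of the 400.** The article says "the sample size calculation was based on a one-way ANOVA comparing the ten independent study groups", with f = 0.20, "a two-sided alpha level of 0.05" and "a desired statistical power of 80 percent". It reports a G*Power minimum of 400 and says that the calculation was deliberately confined to the baseline comparison.
- **Step to 500.** "To account for expected attrition at follow-up, the planned sample size was increased to at least 500 participants".
- **Attrition.** The article cites an earlier study that used the same vignettes and had 55.9% follow-up completion. It continues "Assuming a conservative attrition rate of approximately 40 to 45 percent" and arrives at about 275 to 300 people.
- **Claim about that number.** "which remains adequate for the planned longitudinal and within-subject analyses".

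Three other sections bear on this. Outcomes (2.4.2) makes within-subject stability part of the primary outcome. Planned statistical analysis (2.5.2) gives the within-person methods separately for the two conditions. Data access and management (2.6) says of the contact needed for follow-up: "Providing an email address will not be mandatory for participation in the study".

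**The concern.** Three statements in one paragraph do not fit the figures around them.

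1. The step from 400 to 500 is explained by attrition, but no usual inflation formula links 400, 40–45% and 500. The 400 also belongs to a baseline analysis, which loss at follow-up cannot shrink.
2. The follow-up number is declared adequate, but no effect size, precision target or power is given for any longitudinal or within-subject analysis. This is not detail left to an analysis plan: the article makes a positive claim about the sample and does not support it.
3. The attrition range is called conservative, although it only brackets the loss seen in the cited study.

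Stability over time is part of the primary outcome. A reader told that the follow-up sample is adequate may take a non-significant comparison of stability across the ten groups as evidence that the groups do not differ.

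**Working it through.** **Inputs (section 2.5.1 unless noted).** k = 10 groups; f = 0.20; alpha = 0.05; power 80%; required N = 400; planned N = 500; attrition 40–45%; completion in the cited study 55.9%, so loss = 1 − 0.559 = 44.1%.

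**Step 1: reproduce the 400.** One-way ANOVA power from the noncentral F distribution, with df1 = k − 1 = 9, df2 = N − 10 and noncentrality λ = N·f². At N = 400, λ = 400 × 0.04 = 16 and power = 0.8003. This is the smallest N that reaches 0.80, so the plan's figure reproduces exactly.

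**Step 2: reproduce the follow-up number.** 500 × (1 − 0.45) = 275 and 500 × (1 − 0.40) = 300. Both reproduce. At the cited rate, 500 × 0.559 = 279.5.

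**Step 3: what loss does 500 offset?** 1 − 400/500 = 20%. To retain 400 after a loss d, N = 400/(1 − d), rounded up:

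| Loss d | N needed to retain 400 |
|---|---|
| 20% | 500 |
| 40% | 667 |
| 44.1% (cited study) | 716 |
| 45% | 728 |

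The incorrect variant 400 × (1 + d) gives 560–580 at 40–45%, so it does not explain 500 either.

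**Step 4: the follow-up number under the plan's own criterion.** Same formula, f = 0.20. The per-condition rows assume a 1:1 split (275/2 ≈ 138; 300/2 = 150).

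| N | λ = 0.04N | Power, ten groups | f detectable at 80% |
|---|---|---|---|
| 500 | 20 | 0.90 | – |
| 300 (both conditions) | 12 | 0.65 | 0.23 |
| 275 (both conditions) | 11 | 0.60 | 0.24 |
| 150 (one condition) | 6 | 0.32 | 0.33 |
| 138 (one condition) | 5.52 | 0.29 | 0.35 |

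**Step 5: a test closer to those planned.** For a paired comparison (paired t approximation, two-sided 0.05, 80% power), the detectable standardised change is about 0.23–0.24 with 138–150 people in a condition. With equal groups, each group-by-condition cell has 275/20 to 300/20, about 14–15 people, and the detectable change is about 0.78–0.81.

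**Step 6: HP 4 (section 1.1).** This hypothesis contrasts less with more clinical exposure, not the ten groups. As a two-level contrast with one degree of freedom, at the same f = 0.20 and with an equal split (both assumptions), power is 0.91–0.93 at 275–300 and 0.65–0.68 at 138–150.

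**Step 7: is 40–45% conservative?** The cited loss of 44.1% lies near the top of the range, so the 40% end is more favourable than the only evidence offered. Section 2.6 adds a second filter, the optional email address. The article gives no figure for how many will leave one, so the extra loss cannot be sized.

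**The case against.** The strongest defence is that the paragraph contains no false sum. The 400 reproduces, so do 275 and 300, and the article discloses the expected loss openly. A reader might infer that the plan promises 400 at follow-up, or that its baseline comparison is short because of attrition. The document supports neither. It never says that 400 will remain, and 500 at baseline exceeds the 400 it derived. It follows that 667–728 is not a corrected target: it would be one only if 400 were the follow-up requirement, and no follow-up requirement is set.

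It is also fair to say that f = 0.20 was chosen for differences in baseline ratings. Section 2.5.2 plans Wilcoxon tests, correlations and consistency indices on participant summaries, along with mixed models that use all available ratings. These could have more or less power than the ANOVA, and the article gives no correlation or effect size to settle it. A single paired test within a condition may be well served. A reader might conclude that the within-subject aim as a whole, HP 4 included, has 30% or 60–65% power. Those figures describe only a ten-group comparison at f = 0.20, and Step 6 shows that HP 4's contrast can do much better.

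Finally, the Discussion (section 3) concedes self-selection through the voluntary email, and section 2.5.2 plans attrition analyses. Neither sizes the added loss.

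These points limit the size of the problem. They do not supply a reason for the step to 500, a basis for the adequacy claim, or grounds for the word conservative.

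**Conclusion.** The point holds as a misstatement about the sample size, not as a shortfall in the baseline calculation.

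- The increase to 500 offsets 20% loss, less than half of the 40–45% it is said to cover, and is applied to a baseline requirement that follow-up loss does not touch.
- Adequacy at 275–300 is asserted without support. By the only criterion the plan states, that number has 60–65% power rather than 80%. If the ten groups were compared within one condition, power would be about 29–32%. Both figures are illustrative and rest on f = 0.20 carrying over to follow-up, equal groups and, for the second, a 1:1 split.
- The attrition rate is in line with the cited study and therefore not conservative; the optional email may raise the loss further.

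The documents do not support reclassifying the group-level stability analyses as exploratory: they are part of the stated primary outcome, and the power figures come from a test that is not the planned one.

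One caution on the 0.90 at N = 500. It assumes that all 500 contribute to the stated ANOVA. Section 2.5.1 defines the outcome for sizing as the 1–9 rating in the No-C-SSRS condition, which about half of the participants would provide; at N = 250 the same formula gives 0.55.

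**What to change.** Reword the attrition paragraph of section 2.5.1:

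1. State 500 as the baseline recruitment target, with power of about 0.90 for the stated ten-group ANOVA if both conditions contribute. Remove attrition as its rationale.
2. Delete the word conservative. Say that about 275–300 people (roughly 138–150 per condition) are expected at follow-up, or fewer, because the email address is optional.
3. Replace the adequacy claim with what that number delivers for the planned within-subject analyses: for example, a paired standardised change of about 0.23–0.24 per condition at 80% power. Marked as illustrative, add 60–65% power pooled, or about 29–32% per condition, for a ten-group comparison at f = 0.20.
4. Say that a non-significant ten-group comparison of stability will not be read as evidence of no difference. Keep HP 4's exposure contrast separate from the ten-group figures.

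If the investigators want a powered follow-up analysis instead, they should first set a target for it (power or interval width) and divide the resulting N by (1 − d).

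Cost: rewording only, with no extra participants. The stated properties of the follow-up sample become less favourable.

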#### Planned statistical analysis

2.5.2

Analyses will examine discrepancies in suicide risk assessment across participant groups and over time to identify factors associated with variability. Descriptive statistics will summarize sociodemographic and professional characteristics of the sample, distribution of risk ratings, and follow-up completion rates. Given the hierarchical structure of the data, with multiple vignette ratings nested within participants, mixed-effects regression models will constitute the primary analytical approach. Random intercepts will be specified for participants to account for repeated ratings within individuals and, when appropriate, for vignettes to account for shared variance attributable to scenario characteristics. Fixed effects will include study group, experimental condition (C-SSRS vs. No-C-SSRS), time (baseline vs. follow-up), and their interactions.

Ratings collected on the 1 to 9 scale will be treated as ordinal variables. Accordingly, ordinal mixed-effects models will be used as the primary approach, whereas linear models treating the scale as continuous will be conducted only as sensitivity analyses to ensure robustness of findings. To evaluate potential bias related to categorization thresholds, sensitivity analyses will include alternative binning strategies (e.g., 1–2 vs. 3–7 vs. 8–9) and models using the full 1–9 scale without categorization.

To quantify inter-rater agreement across raters for each vignette, Krippendorff’s alpha will be used as the primary agreement index, as it is appropriate for multi-rater settings with potentially unbalanced data. Weighted kappa coefficients will be computed only in supplementary pairwise comparisons to facilitate interpretability relative to commonly reported agreement metrics. Within-person analyses will evaluate the stability of participants’ overall level and pattern of risk estimates across time using different vignette sets drawn from the same risk-calibrated pool. These analyses do not represent test–retest reliability of identical stimuli but rather the temporal consistency of risk perception. Because different vignettes of the same risk category will be administered at baseline and follow-up, within-person analyses will be conducted on participant-level summary indices (e.g., central tendency of ratings and distribution of risk categories across vignettes at each time point) rather than on vignette-level paired comparisons. For the No-C-SSRS condition, paired non-parametric tests, such as the Wilcoxon signed-rank test, and correlation analyses will be used. For the C-SSRS condition, indices of temporal consistency will be computed to evaluate the stability of participants’ overall tendency to classify scenarios into risk categories across time, rather than agreement on identical stimuli.

The mixed-effects framework described above will also be used to examine interaction effects. Pre-specified interaction terms will examine whether differences in risk estimation vary as a function of demographic and professional variables (e.g., age, gender, years of clinical experience, prior suicide-specific training) across study group and experimental condition. In addition, to control for inflation of Type I error due to multiple comparisons, p-values from secondary analyses will be adjusted using the false discovery rate approach.

Missing data will be handled under a missing-at-random assumption using maximum likelihood estimation within mixed-effects models, which allows inclusion of all available observations without listwise deletion. Attrition between baseline and follow-up will be examined descriptively, and sensitivity analyses will compare participants who completed follow-up with those who did not. Predictors of attrition will be explored to assess potential systematic differences between completers and non-completers.

